### Sample size

To calculate the sample size, the method of distinguishing between the means was used, being n = (α + β) 2 σ2/d2. The values of α = 0.05 and β = 0.80 were adhered to, for which, according to the Gaussian curve table, values of 1.64 and 0.84, respectively, were used. The difference between the means was obtained through the pilot study, and a variable considered for the calculation was quality of life, in which an average of the difference between all the scales in the before and after periods was found. This value of the expected selection was 6.15 ± 9.4. The expected variance (σ2) was 89.49. At the end of the analysis, after inclusion of a 30% margin of sample loss, a sample of 19 patients was selected for each group. Figure 1 shows the flow diagram of the study participants.

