This study protocol describes a randomized controlled trial of Pilates solo and belly dance (three times per week) for women after the diagnosis of breast cancer and compare its effects with a control group without intervention. The hypothesis is that the Pilates solo and belly dance protocol will promote improvement in primary (quality of life) and secondary (psychological and physical) outcomes in women after the diagnosis of breast cancer, providing a beneficial activity option for women with breast cancer. Our second hypothesis is that Pilates will lead to better improvements in the physical variables and belly dance will improve psychological variables.

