#### Statistical analysis

First, a spreadsheet will be created using the Excel 2016 software (Microsoft, Redmond, WA, USA), from which the data will be transferred to IBM SPSS Statistics version 20.0 software (IBM, Armonk, NY, USA) for analysis. Descriptive statistics (mean, standard deviation, and percentage) for the characteristics of the sample will be computed. To investigate the relationship between general and health information of the control and experimental groups, chi-square or Fisher’s exact tests will be used. To analyze differences in the experimental and control groups in the baseline, postintervention, and maintenance periods, two-way analysis of variance with repeated measures and Holm-Šídák comparison tests will be conducted. Confounder variables will be considered in the analyses as type of treatment, type of surgery, age, and weight status. The analysis will be performed according to the protocol and intention to treat, meaning that all the patients will be evaluated according to the randomization process. Missing data will be handled using the multiple imputation method. The significance level of 5% will be two-sided.

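### The 19 per group comes from a one-sided, single-group before-after formula, while the trial compares independent arms two-sided, so it does not deliver 80% power for the comparison with control

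*Protocol article*

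**What the plan says.** All inputs stand in the Sample size section of the protocol article.

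- Formula: "the method of distinguishing between the means was used, being n = (α + β) 2 σ2/d2". The exponents were flattened when the text was extracted.
- Error rates: "The values of α = 0.05 and β = 0.80 were adhered to". The 0.80 is labelled β but is the power, since 0.84 is the normal quantile for 80%.
- Quantiles: "according to the Gaussian curve table, values of 1.64 and 0.84, respectively, were used".
- Source of the effect: the pilot study, in which "an average of the difference between all the scales in the before and after periods was found".
- Effect and spread: "This value of the expected selection was 6.15 ± 9.4", with a variance of 89.49.
- Result: "after inclusion of a 30% margin of sample loss, a sample of 19 patients was selected for each group".

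Other sections describe a different comparison. Study design sets out a single-center, three-arm randomized trial with a control group. Statistical analysis plans a two-way repeated-measures analysis of variance comparing experimental and control groups, with Holm-Šídák tests, and adds: "The significance level of 5% will be two-sided".

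**The concern.** The calculation and the planned test differ in two respects. First, a formula of the form (z + z)² σ²/d² without a factor 2 gives the number needed to show that one group's mean change differs from zero. The variance of a difference between two independent arms of equal size is twice that of one arm's mean, so a between-arm comparison needs twice the number. Second, 1.64 belongs to a one-sided 5% test, while the analysis section fixes a two-sided test, for which the quantile is 1.96.

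Two further features push the same way. The 6.15 is an uncontrolled change, with no control-group change subtracted. And the margin for loss appears to have been added by multiplying by 1.3, which does not leave the required number after 30% are lost.

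At stake is the statement that the trial has 80% power for its primary outcome. If that figure stands, a non-significant comparison with control could be taken as evidence that the interventions do not help, when the trial had at best about an even chance of detecting the difference it was sized on.

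**Working it through.** **1. Reproducing the plan's figure.** Inputs: z = 1.64 and 0.84, d = 6.15, σ² = 89.49 (SD 9.46; the printed 9.4 is a rounding, and 9.4² = 88.36 leads to the same 19).

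n = (1.64 + 0.84)² × 89.49 / 6.15² = 6.1504 × 89.49 / 37.8225 = 14.55

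14.55 × 1.3 = 18.9, hence 19. This matches.

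**2. Could another reading give 19?**

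| Reading | n before loss | × 1.3 | ÷ 0.7 |
|---|---|---|---|
| One group, one-sided | 14.55 | 18.9 | 20.8 |
| The 2 as a multiplier of an unsquared sum | 11.7 | 15.3 | 16.8 |
| Two groups, one-sided | 29.1 | 37.8 | 41.6 |
| One group, two-sided | 18.5 | 24.1 | 26.5 |

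Only the first row uses the stated 1.64 and the stated 30% margin and arrives at 19. The last row also rounds to 19, but only with 1.96 and no margin, which is not what the section says. The flattened exponent therefore leaves no real doubt.

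**3. The margin for loss.** 19 × 0.70 = 13.3, so about 13 complete, fewer than the 14.55 that the formula itself asks for. Inflating by 1/(1 − 0.30) gives 14.55 / 0.70 = 20.8, that is 21.

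**4. The number for the comparison that is planned.** Two independent arms, two-sided 5%, 80% power, same d and σ²:

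n = 2 × (1.96 + 0.84)² × 89.49 / 6.15² = 2 × 7.84 × 89.49 / 37.8225 = 37.1, so 38 per arm

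The noncentral t distribution gives 39 (38 reaches 79.9%). With 30% loss: 38 / 0.70 = 54.3 and 39 / 0.70 = 55.7, so about 55 enrolled per arm.

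**5. Power with 19 per arm.** Assumptions: the between-arm difference in change is 6.15 (control change of zero), the SD of change is 9.46 in each arm, and the comparison is unadjusted. Noncentrality is 6.15 / (9.46 × √(2/n)) with 2n − 2 degrees of freedom.

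| Evaluable per arm | Noncentrality | Power, two-sided 5% | Difference detectable with 80% power |
|---|---|---|---|
| 13 | 1.66 | 36% | 10.8 |
| 14 | 1.72 | 38% | 10.4 |
| 19 | 2.00 | 50% | 8.8 |

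The normal approximation gives 38%, 41% and 52%.

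**6. Sensitivity.**
- One-sided testing, contrary to the analysis section: 49%, 51% and 63% at 13, 14 and 19 per arm.
- Baseline adjustment, with 9.46 as the SD of change and an assumed pre-post correlation r: the residual SD is 9.46 × √((1 + r)/2). For r from 0.3 to 0.7 the t-based power is 56–68% at 19 per arm and 41–54% at 13–14. The normal approximation gives 58–70% and 44–57%.
- Multiplicity: if the Holm-Šídák family is the three pairs of arms (an assumption), the first step is at 1 − 0.95^(1/3) = 0.017, and power there is 20%, 22% and 32% at 13, 14 and 19 per arm.

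**The case against.** **The power figures are conditional.** The document gives no between-arm difference, no control change and no pre-post correlation. Using 6.15 as the between-arm difference borrows an uncontrolled change for a purpose it does not serve. The Primary outcome measure section also names another threshold, 2% of baseline scores, so the target is not wholly settled. This stands: 36–50% is what the plan's inputs imply under stated assumptions, not the trial's known power. A zero control change is the generous choice, though, since the control arm is offered three meetings, including stretching and self-esteem.

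**The planned analysis is not a t-test on completers.** It is a repeated-measures analysis with confounders considered, intention to treat, multiple imputation, and data collection from patients who discontinue. This stands in part. Power could exceed the unadjusted figure, but baseline is not among the named confounders, and adjusting for it does not reach 80% over the assumed correlations. Imputation does not restore lost information, and even 19 complete cases per arm give 50%.

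**The margin for loss is a small matter.** True: 19 against 21, and the multiplication by 1.3 is inferred from the result.

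**The Holm-Šídák family is undefined, and its first step is the strictest.** Also true, so the 20–32% is a lower bound under an assumed family.

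**Stronger readings to avoid.** A reader might infer that the hypothesis "Our second hypothesis is that Pilates will lead to better improvements in the physical variables", with its counterpart for belly dance, is still more underpowered. It concerns physical and psychological variables; the sample-size section claims no power for it and gives no effect or SD, so the document supports no figure. A reader might also infer much lower power for any single quality-of-life scale. No single-scale SD is given, and the section defines its variable as an average over all scales. Finally, a sample-size error neither biases the estimates nor inflates the type I error, and nothing in the document says that a null result will be read as no benefit.

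**Conclusion.** The point holds. The 19 per group is exactly a one-sided, one-group before-after number, and it contradicts the article's own design and its two-sided test, so the 80% power is wrong as written. That part needs no assumption beyond the stated inputs.

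The size of the shortfall does rest on assumptions: 6.15 as the between-arm difference in change, 9.46 as the SD of change, and an unadjusted pairwise comparison. Under them the trial falls about 30 percentage points short of 80% with no loss and 42–44 points short after 30% loss, and enrols 19 per arm where about 55 would be needed. Improvement among controls or a multiplicity adjustment would lower the power. Baseline adjustment would raise it, but not to 80% for correlations of 0.3 to 0.7. This must be corrected, because it is the only justification given for the trial's size.

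**What to change.** Rewrite the Sample size section with the two-sample, two-sided formula, 2 × (1.96 + 0.84)² σ²/d². State the between-arm difference assumed and whether σ is the SD of change, label 0.80 as power, and inflate by 1/(1 − 0.30).

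Then choose one of two courses. The article reports that the trial is still enrolling, so the target could be raised towards about 55 per arm; that is costly at one center. Or 19 per group is kept and the claim is restated: roughly 36–50% power for 6.15 points under the assumptions above, with 80% power only for about 8.8 points (19 evaluable per arm) to 10.8 points (13 evaluable per arm). In that case, commit to reporting between-arm estimates with confidence intervals and to not reading non-significance as absence of effect.

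The second course costs wording only. Its price is a less favourable power statement.

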### Assessment

#### Primary outcome measure

The main aim of the study is to evaluate the impact of a 16-week Pilates solo and belly dance protocol on quality of life (≥ 2% of the baseline scores) in patients with breast cancer undergoing clinical treatment. Quality of life is the primary outcome at all time points of the study, namely baseline; postintervention; and 6, 12, and 24 months after intervention. Quality of life will be the primary outcome because it involves all the physical and psychological aspects of the life of women with breast cancer. Therefore, the maintenance collection will take place considering the modification in quality of life and other outcomes that the Pilates solo and belly dance intervention can promote in these women.

The primary outcome of quality of life will be investigated by using the European Organization for Research and Treatment of Cancer Quality of Life Questionnaire C30 (EORTC QLQ-C30) [39]. This instrument was created by the European Organization for Research and Treatment of Cancer (EORTC) in 1986, and this is the third version. Validated for the cancer population by Michels et al. [40], with Cronbach’s α values of 0.72 for global health, 0.86 for the functional scale, and 0.81 for the symptomatic scale.

The instrument consists of 30 questions, being multidimensional and self-applied. Its objective is to evaluate the quality of life in patients with cancer in the last 4 weeks. It presents five functional scales (physical, functional, emotional, social, and cognitive), a scale on global health status, three symptom scales (fatigue, pain, and nausea/vomiting), and six additional symptom items (dyspnea, appetite, constipation, diarrhea, and financial difficulties). The answers are presented in the form of a Likert scale following the classification 1 = not at all, 2 = a little, 3 = quite a bit, and 4 = very much. The only exception applies to the global health scale. This is composed of two questions that ask the patient to rate both health and quality of life in the last week according to grades of 1 to 7. In this case, 1 would be a poor quality of life and 7 a good quality of life.

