The EORTC QLQ-C30 is complemented by specific cancer modules. In this study, the breast cancer module, QLQ BR-23, validated for the Portuguese language by Michels et al. [40], with Cronbach’s α values of 0.78 and 0.83, will be used. The QLQ BR-23 consists of 23 questions incorporated into multi-item scales. It measures the functional scales (body image, sexual functioning, sexual enjoyment, and future perspective) and symptom scales (systemic therapy side effects, arm symptoms, breast symptoms, and upset by hair loss). Classifications are also in the range of 0 to 100, where values ​​closer to 100 for the functional scale indicate better patient functionality and values ​​closer to 100 for the symptom scales show higher presence of symptoms.

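### The effect and variance behind 19 per group come from a pilot change averaged over all quality-of-life scales, a score the protocol neither defines nor analyses, so the 80% power cannot be tied to any defined outcome

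*Protocol article*

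**What the plan says.** The Sample size section of the protocol article uses the formula "n = (α + β) 2 σ2/d2", with normal quantiles of 1.64 and 0.84 standing for a 5% level and 80% power. The variable is quality of life in the group's pilot study, for which "an average of the difference between all the scales in the before and after periods was found". The result is given as 6.15 ± 9.4, and "The expected variance (σ2) was 89.49". With 30% added for losses, the section arrives at 19 women per group.

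The Primary outcome measure section names two instruments, the QLQ-C30 and the QLQ-BR23. Of the first it says: "It presents five functional scales (physical, functional, emotional, social, and cognitive), a scale on global health status, three symptom scales", followed by six further symptom items. For the second it lists four functional and four symptom scales. It also says that values near 100 mean better function on the functional scales, whereas values "closer to 100 for the symptom scales show higher presence of symptoms". It describes no score that combines the scales.

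The Statistical analysis section plans a two-way repeated-measures analysis of variance with Holm-Šídák comparisons. It mentions no averaged score either.

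**The concern.** A power statement belongs to a particular score: the difference and the SD in the formula must be those of the quantity to be tested. Here both come from an average over all scales, and the article nowhere makes that average an outcome. A reader therefore cannot say for which result the trial has 80% power, nor what a 6.15-point difference means on any scale that will be reported.

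Two gaps make the inputs hard to interpret. The scales run in opposite directions, and the text does not say whether the symptom scales were reversed before averaging. Nor does it say whether 9.4 is a spread between women or between scales.

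If a quality-of-life comparison turns out null, the stated power could be cited as evidence that a real effect would have been found, when that power was worked out for something else.

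**Working it through.** **1. Reproduce the plan's figure.** Inputs from the Sample size section: quantiles 1.64 and 0.84, variance 89.49, difference 6.15, allowance 30%.

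- n = (1.64 + 0.84)² × 89.49 / 6.15² = 6.1504 × 89.49 / 37.8225 = 14.55
- 14.55 × 1.3 = 18.92, rounded up to 19
- √89.49 = 9.46, which agrees with the stated 9.4 apart from rounding

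The arithmetic is sound. The question is what 6.15 and 89.49 measure.

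**2. Compare the inputs with the outcome.** By the article's own count the QLQ-C30 has 5 + 1 + 3 + 6 = 15 scales and items, and the QLQ-BR23 has 4 + 4 = 8, making 23 in all. The planning input is one average over all the scales. The Primary outcome measure section has only the separate scales, and the Statistical analysis section adds no composite. The two do not meet.

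**3. What ±9.4 could be.** The wording allows three readings.

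- (a) The between-patient SD of each woman's average change over the scales.
- (b) The spread of mean changes across scales. This is not a between-patient SD and cannot serve as σ in the formula.
- (c) An average of the SDs of the individual scales. It is then already a typical single-scale SD, and no inflation applies.

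**4. Size under reading (a) only.** Assume k scales with equal SDs and a common correlation ρ between their changes, and hold the difference at 6.15. None of ρ, the equality of SDs or the pilot's k is in the document; k = 15 and k = 23 are taken from the instruments described.

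- Single-scale SD = 9.46 × √[k / (1 + (k − 1)ρ)]
- Power by the plan's formula = Φ(6.15 × √14.55 / SD − 1.64)

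| ρ | SD, k = 15 | SD, k = 23 | Power, k = 15 | Power, k = 23 |
|---|---|---|---|---|
| 0.8 | 10.5 | 10.5 | 72.5% | 72.2% |
| 0.6 | 12.0 | 12.0 | 62.7% | 62.1% |
| 0.5 | 13.0 | 13.1 | 56.8% | 56.0% |
| 0.3 | 16.1 | 16.5 | 42.9% | 41.5% |
| 0.2 | 18.8 | 19.5 | 34.8% | 33.1% |

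With SD 9.46 the same expression returns 80%. That is also the answer under reading (c).

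**5. Separate this from the formula problem.** The quantile 1.64 is one-sided, whereas the Statistical analysis section says "The significance level of 5% will be two-sided". The formula also lacks the factor 2 needed to compare two groups. Accepting 6.15 and 9.46 as they stand, a two-sided two-sample t-test at 5% with 19 per arm has 49.6% power. That fault exists whatever the averaging did. Conversely, correcting the formula while keeping 6.15 and 89.49 would still leave the power attached to an undefined score.

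**The case against.** The strongest reply is that the article is a condensed account. It does not say which score is analysed, and the full protocol or analysis plan may do so. One therefore cannot assert that 9.4 is wrong for that score. This stands, and it limits the point to what the article itself states: the inputs it gives do not correspond to any score it defines.

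A reader might infer that improvements on functional and symptom scales cancelled in the average. The documents do not support this. They are silent on reversal, and the figure itself hints the other way. Of the 23 scales, 10 are better when high and 13 worse when high. With an equal improvement of x points on every scale, an unreversed average would be (10 − 13)x/23 = −0.13x, or (6 − 9)x/15 = −0.2x for the QLQ-C30 alone. An absolute value of 6.15 would then need x of about 47 or 31 points. Unequal improvement could still produce 6.15, so this is not proof of reversal. Had cancellation occurred, 6.15 would understate the change on individual scales, which acts against a loss of power.

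A reader might also infer that power is certainly below 80% because of the averaging, or that some minimum loss is established. Neither follows. The table holds under one of three readings, with assumed ρ, k and equal SDs, and with the difference fixed.

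Lastly, it can be said that the formula problem alone already defeats the 80% claim. That is true, but repairing the formula would not repair the inputs.

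**Conclusion.** The point holds as a fault in the sample-size inputs, not in the arithmetic. The values 6.15 and 89.49 describe a pilot change averaged over all quality-of-life scales. The article defines no such score as an outcome and analyses none, so its 80% power cannot be tied to a defined score.

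The size and direction of the error are unknown. Under reading (a), with assumed correlations from 0.8 to 0.2, the single-scale SD would be about 10.5 to 19.5 and power by the plan's formula about 72% down to 33%. Under reading (c) this issue causes no loss. Under reading (b) the 9.4 is not a usable SD and no power can be computed from it. The matter is worth correcting while the trial is enrolling, since the stated power will shape how a null quality-of-life result is read.

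**What to change.** In the Sample size section, replace 6.15 ± 9.4 with the pilot mean and between-patient SD of change for one score that the trial will analyse as primary. Then restate the power that 19 per group gives for it, or the difference detectable with 80% power.

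Alternatively, if the all-scale average is truly intended, define it as the primary score with symptom scales reversed, recompute its pilot mean and between-patient SD, and analyse that score. If neither is done, remove the 80% claim.

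The cost is a small re-analysis of the group's own pilot data and a rewritten paragraph, with a stated power that may look less favourable. Enrolment does not have to change. The formula should be corrected in the same revision, but that is a separate repair.

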**Fig. 1 Fig1:**
[figure not shown]
Flow diagram of the study participants according to Consolidated Standards of Reporting Trials (CONSORT 2010)

### Randomization and blinding process

The randomization of the sample will be performed by one of the researchers, who should have access to a list of patients with breast cancer (stages 0–III) who were receiving adjuvant treatment with hormone therapy at CEPON in the past 3 years, with the intention to achieve adequate participant enrollment to reach the target sample size. From this list, randomization will be carried out via a website (http://www.randomization.com), which will predict the allocation of patients in the three groups: group A, intervention with belly dance; group B, intervention with Pilates solo; and group C, control group that will be requested to maintain routine activities. The randomization will be stratified by age, dividing the patients between those younger and those older than 60 years of age, considering those older than 60 years of age, according to the Brazilian Statute of the Elderly, established by Law No. 10,741, dated October 1, 2003.

The data from the patients will be maintained only with the principal researcher to protect confidentiality before, during, and after the trial. Because the protocol is difficult to blind for the subjects and the instructors inasmuch as there is no proper way to perform sham physical exercise, all the data analysis will be performed by an external researcher. In this way, at least the data analysis will not be subject to interference.

